## Abstract

**Background:**

Sub-Saharan Africa remains the region most affected by the HIV epidemic, with Zambia experiencing a substantial burden of disease. Young people with HIV are disproportionately impacted. Emerging adulthood (ages 18-24 years) is characterized by increasing independence, risk-taking behaviors, identity exploration, and changing social supports, all of which may impact HIV self-management, including medication adherence and retention in care. Substance use may further undermine HIV outcomes. Innovative interventions targeting HIV self-management and substance use reduction among Zambian young people are urgently needed.

**Objective:**

This study aims to develop and pilot a multicomponent mobile health (mHealth) intervention to improve HIV self-management and reduce substance use among young people in Zambia. We will adapt the 4-session in-person Healthy Choices intervention for mobile delivery (mobile Healthy Choices [mHC]) to increase access and delivery. We will also develop motivational text messaging (MTM) to enhance intervention impact. Both components will be delivered using the Computerized Intervention Authoring System. Using the multiphase optimization strategy (MOST) framework, we will assess preliminary efficacy and identify the most effective components.

**Methods:**

The study includes 3 phases. Phase 1 will involve conducting focus groups with Zambian young people with HIV to explore barriers and facilitators of HIV self-management and substance use to inform intervention adaptation. Phase 2 will involve adaptation and beta testing of mHC and MTM for functionality and feasibility using a community advisory board. Phase 3 will consist of a pilot trial using the MOST framework to evaluate feasibility, acceptability, and preliminary efficacy of intervention components. A total of 100 young people with HIV will be randomized to one of four experimental conditions: (1) standard antiretroviral therapy (ART) counseling (SAC), (2) mHC+SAC, (3) MTM+SAC, and (4) mHC+MTM+SAC. Primary outcomes will include feasibility, acceptability, ART adherence, viral suppression, and substance use. Feasibility and acceptability will be assessed through paradata of use patterns and the System Usability Scale. Participants will complete assessments at baseline and at 3- and 6-month follow-up visits. Biomarkers of ART adherence and/or sexually transmitted infections will also be collected.

**Results:**

Recruitment for this study began in May 2024 for phase 1. Focus group discussions were completed with 48 young people with HIV in July 2024. Phase 3, the pilot feasibility trial, began in June 2025. Upon project completion, we will have developed an innovative mHealth intervention to support HIV self-management and reduce substance use among Zambian young people with HIV.

**Conclusions:**

This study addresses a critical problem—suboptimal ART adherence, substance use, and challenges with HIV self-management—among young people with HIV in Zambia. We are developing 2 technology-based, theory-driven intervention components aimed at improving HIV self-management and substance use outcomes. If successful, this study will pave the way for scale-up of mHealth interventions to improve HIV care outcomes among young people with HIV in Zambia and other low-resource settings.

**Trial Registration:**

ClinicalTrials.gov NCT06415357; https://clinicaltrials.gov/study/NCT06415357

**International Registered Report Identifier (IRRID):**

DERR1-10.2196/99714

## Introduction

### Background

Despite significant advances in HIV prevention and treatment, HIV and AIDS remain a leading cause of morbidity and mortality in sub-Saharan Africa (SSA) [1]. In 2021, Zambia’s adult HIV prevalence (10.8%) was the seventh highest globally [1], with more than 15,000 new infections among youth aged 15 to 24 years [2]. Young people with HIV experience substantial disparities across the HIV care continuum, including lower antiretroviral therapy (ART) adherence, missed clinic visits, and lower viral suppression than older individuals [3,4]. Interventions designed for youth are crucial to improve adherence and viral suppression and to reduce mortality.

Young people with HIV are in emerging adulthood, a developmental stage marked by increasing independence, identity exploration, and risk-taking behaviors that may compromise HIV self-management [5]. Young people with HIV often exhibit poor HIV management, including suboptimal medication [6] and appointment adherence, limited engagement in health care [7], risky sexual behavior, alcohol use [8], and other substance use [9]. Zambian youth have the highest rate of regular alcohol use among 73 low- and middle-income countries [10] and the highest prevalence of cannabis use in Africa (37.2%) [11]. Alcohol use has synergistic and additive effects on HIV comorbidities [12] and accelerates HIV disease [13]. It is linked to increased HIV transmission [14], poor ART adherence [15], and worse outcomes across the treatment cascade [16]. In Zambia, commonly used substances include marijuana, cigarettes, opiates, cocaine, and inhalants [17], and 47% of youth have used a psychoactive substance [18].

Stigma is a well-documented barrier to health-seeking behaviors [19], engagement with the health care system [20], and adherence to treatment [21] across health conditions, including HIV [22]. For young people with HIV, stigma contributes to risky sexual behavior and substance use [23], reduces social support [24], and exacerbates mental health concerns such as depression [25]. Young people with HIV in Zambia widely experience HIV-related stigma across socioecological levels. Together, stigma and mental health are important targets for HIV interventions.

Strikingly, few interventions address self-management of both HIV and substance use in young people with HIV [26]. Healthy Choices (HC) is one of the few interventions that has demonstrated improvements in viral load and alcohol trajectories in young people with HIV [27,28]. HC also showed improvement in depression [29], marijuana use [28], and HIV-related stigma [30]. HC is a 4-session program that integrates motivational interviewing (MI) tailored for young people with HIV [27,31]. However, in-person HC can be limited by time, clinic engagement, and implementation barriers. Delivering HC via mobile health (mHealth) may increase access and engagement, reduce cost and time for youth and staff, and support implementation in clinics.

mHealth has been rapidly expanding across African countries, with widespread success in delivering health services [32]. Mobile connections in Zambia were equivalent to 91.4% of the total population in early 2022 [33]. SMS text messaging is inexpensive, nonintrusive, and widely integrated into the daily lives of youth in SSA [34]. Motivational text messaging (MTM) interventions have improved ART adherence and viral suppression among young people with HIV in SSA [35]. MTM offers a low-cost, sustainable, and youth-friendly way to extend the reach of HC sessions.

This study will adapt HC for mobile delivery and integrate MTM to improve HIV self-management and reduce substance use among young people with HIV in Zambia. It will develop and pilot a scalable, youth-friendly intervention to improve ART adherence, engagement in care, and health outcomes.

### Study Aims

We propose to develop and pilot a multicomponent mHealth intervention to improve HIV self-management and reduce substance use among young people with HIV in Zambia. First, we will adapt the 4-session HC intervention for mobile delivery and develop MTM to enhance the impact of mobile HC (mHC). Both components will be delivered using the Computerized Intervention Authoring System (CIAS). Second, we will conduct a pilot trial using the multiphase optimization strategy (MOST) framework to evaluate the feasibility, acceptability, and preliminary efficacy of intervention components and identify the most promising intervention component or combination of components. This study will lay the groundwork for a future fully powered efficacy trial and may provide a scalable model for improving outcomes among young people with HIV in Zambia.

### Theoretical Frameworks for Behavioral Change

The information-motivation-behavioral skills (IMB) model and the socioecological model (SEM) will serve as the conceptual frameworks. Both theoretical models have been applied to HIV health behaviors [36] and ART adherence [37]. Although the IMB model focuses on individual-level determinants of behavior, the SEM captures the broader individual-, social-, and structural-level factors that influence HIV self-management and substance use. The proposed intervention focuses primarily on behavior change at the individual level while also addressing social- and structural-level influences, such as stigma, depression, and barriers to care engagement. According to the IMB model, behavior change results from the joint function of accurate information about risk behaviors (eg, risks of nonadherence to ART and substance use), motivation to change behavior, and behavioral skills to perform the behavior (Figure 1). According to the SEM, health behaviors are influenced by the complex interplay of multilevel factors related to these elements. We will develop intervention content to address both individual and multilevel influences to facilitate HIV self-management and reduction of substance use among young people with HIV in Zambia.

**Figure 1 figure1:**
[figure not shown]
Integrated application of the information-motivation-behavioral skills model and the socioecological model for antiretroviral therapy (ART) adherence and alcohol use.

### Intervention Components

#### Mobile Healthy Choices

mHC is a 4-session computer-delivered intervention. CIAS supports MI-based intervention delivery by allowing participant choices and branching to tailored content throughout the session. For instance, a participant indicating high levels of motivation for improving HIV management will be routed to different content than a participant with lower motivation. During sessions, specific strategies to overtly communicate acceptance and support autonomy are included to address stigma and strengthen motivation for change. In session 1, young people with HIV choose 1 of 2 primary target behaviors (HIV self-management or alcohol use). Young people with HIV will focus on the selected behavior, though other behaviors such as sexual risk, stigma, depression, and other substance use will be addressed during sessions. The virtual counselor (avatar) will use standard MI techniques to elicit the participant’s perspective on the selected problem and build motivation for change by eliciting and reinforcing change talk. The avatar will deliver feedback based on responses to prompts within the session and discuss a behavior change plan, and the youth will set the change plan goal. The second session follows the same format for the second behavior. In sessions 3 and 4, the avatar will review the change plan, reinforce motivation and confidence, address barriers through problem-solving, consolidate commitment, and discuss strategies to maintain behavior change [38]. Sessions will also address contextual issues, including stigma.

#### MTM

SMS text messages will consist of motivational statements promoting self-management of HIV and reductions in alcohol use and will be developed based on findings from phases 1 and 2. CIAS will be used to automate and tailor MTM delivery. The system will allow flexibility in message timing and frequency and will automatically record message delivery status. MTM will be sent daily for 2 months, and weekly for an additional 4 months (months 3-6) at times chosen by the participants. MTM content will be tailored on readiness to change, as assessed during mHC session 1. Participants will be informed that mobile phones may be shared or accessed by others and will be advised to review study-related messages only in private settings. All SMS text messages will use neutral, nonidentifying language and will avoid explicit references to HIV, substance use, or mental health concerns. Participants may discontinue MTM at any time. Research staff will be trained to recognize participant distress, substance use concerns, and potential safety risks; participants requiring additional support will be referred to appropriate HIV, mental health, or substance use treatment services available through collaborating clinical sites. All MTM content will be reviewed by the community advisory board (CAB) before trial launch to ensure cultural appropriateness, clarity, and privacy protection.

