#### Phase 3: Pilot MOST Design–Based Trial

##### Overview

We will evaluate the feasibility, acceptability, and preliminary efficacy of adapted intervention components to improve HIV self-management and substance use in a MOST design–based trial (ClinicalTrials.gov NCT06415357). The design is shown in Table 1. The trial will examine the effect of each component and whether the presence or absence of a component has an impact on the performance of other components. An advantage of the MOST framework is its ability to identify intervention components that make significant contributions to overall effectiveness and should therefore be retained in an optimized intervention package. We will use a full factorial design because of its relative simplicity and cost-efficiency [46]. For our trial, there are 2 components, each with 2 levels, resulting in a 2×2 full factorial design with 4 experimental conditions (Table 1). We will use viral suppression as a measure of success (viral load <200 copies/mL) [47] and optimization criterion. We will enroll 100 young people with HIV who are not adherent to ART and report unhealthy alcohol use [48] or any drug use. “Standard ART counseling” will be provided to all participants as a constant component. Young people with HIV will be randomly assigned to 1 of 4 conditions (Table 1). The primary outcome will be ART adherence and HIV viral load. The main effects of the components and interactions between them will be estimated using ANOVA. The goal of this pilot trial is to estimate preliminary effect sizes, evaluate feasibility and acceptability, and identify promising intervention components for inclusion in a future fully powered RCT. This protocol is developed in accordance with the SPIRIT (Standard Protocol Items: Recommendations for Interventional Trials) guidelines (Multimedia Appendix 1).

**Table 1 table1:** Full factorial design with 4 experimental conditions.

Experiment conditions	Standard antiretroviral therapy counseling	Mobile Healthy Choices	Motivational text messaging
1 (n=25)	Yes	Yes	Yes
2 (n=25)	Yes	Yes	No
3 (n=25)	Yes	No	Yes
4 (n=25)	Yes	No	No

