### Data Analysis

We will estimate retention rates overall and per condition and examine differences across conditions using chi-square tests. We will assess differences in acceptability using 2-tailed *t* tests or Mann-Whitney *U* tests. Minimum criteria for acceptability and feasibility will include a mean System Usability Scale score ≥70 and at least 50% of participants responding to MTM at least once and completing at least 2 mHC sessions [51].

To test the main effects and interactions between components using data from the 2×2 factorial study design, we will use ANOVA with effect coding (−1=“no” condition; +1=“yes” condition) rather than dummy coding. The preliminary intervention effects on ART adherence and substance use outcomes will be assessed using linear mixed-effects models, while viral suppression will be analyzed using mixed-effects logistic regression models. Models will adjust for baseline values of the outcome and relevant covariates and will account for repeated assessments over time. Missing data will be handled using full information maximum likelihood estimation. Effect sizes will be estimated for the primary outcomes.

We will make a preliminary selection of components that have achieved main effects. This selection will then be re-evaluated considering any substantial interaction effects to understand how the components work in combination. Depending on the optimization criterion (viral suppression), this will be combined with other information (eg, cost, feasibility, and scalability) to make a final selection of components. This information will inform the development of an optimized intervention package.

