## Results

Recruitment for this study began in May 2024 for phase 1. Qualitative interviews were completed with 48 young people with HIV in July 2024. Qualitative data analysis has been completed, and the results were used to inform intervention adaptation and refinement. In phase 2, our team developed 4 MTM libraries focused on (1) ART adherence, (2) substance use, (3) self-management, and (4) empowerment, containing 76 messages; these messages were reviewed by the youth advisory board and investigator team for refinement. Refined MTM will be delivered to participants through SMS 2.0, an SMS text messaging platform. Our team also developed a 4-session intervention (mHC) to promote ART adherence and substance use reduction using the CIAS (version 3.0). Ten Zambian young people with HIV completed one-on-one beta testing of the intervention components and provided additional feedback to guide refinement. Phase 3, the pilot feasibility trial, began in June 2025. The findings will be disseminated to stakeholders and communities of interest through peer-reviewed journals, academic conferences, and other communication channels.

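### MTM tailoring relies on a readiness score from mHC session 1, which the MTM-only arm never has, so that arm's messages are undefined and any tailoring benefit is aliased with mHC level

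*Protocol article*

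**What the plan says.** In the protocol article, the MTM section under Intervention Components gives the tailoring rule without exception: "MTM content will be tailored on readiness to change, as assessed during mHC session 1". The Abstract (Methods) lists the arms as "1) standard antiretroviral therapy (ART) counseling (SAC), (2) mHC+SAC, (3) MTM+SAC, and (4) mHC+MTM+SAC". Table 1, in the Phase 3 Overview, gives 25 participants per condition, and its condition 3 has MTM but no mHC.

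The Phase 3 Overview describes the two components as "resulting in a 2×2 full factorial design with 4 experimental conditions". It says the trial will examine each component's effect and "whether the presence or absence of a component has an impact on the performance of other components". Data Analysis specifies "ANOVA with effect coding (−1=“no” condition; +1=“yes” condition) rather than dummy coding", so MTM is one two-level factor whatever the mHC level. Selection follows from those estimates: "We will make a preliminary selection of components that have achieved main effects". The selection is then re-evaluated for interactions and combined with cost, feasibility and scalability.

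No section names another source for the readiness score, a default message stream, or a readiness-only module for the MTM-only arm. Data Collection Procedures and Table 2 list intentions, attitudes and motivations as outcome measures but do not connect them to message routing.

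**The concern.** A factorial contrast for MTM is interpretable as the effect of one component only if assignment to MTM means the same intervention with and without mHC. The tailoring input named in the article is produced inside the other component. In the mHC+MTM arm it can exist; in the MTM-only arm it cannot.

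Two things follow. First, the content of the MTM-only arm is undefined as written, so it cannot be replicated from the article whatever tailoring is worth. Second, if that arm's messages differ from those in the combined arm, the difference coincides exactly with the mHC factor. A benefit of tailoring would then look like synergy between the components and would also raise both main effects. These are the quantities used to decide what enters the optimised package. No analysis can separate them afterwards, because no cell has tailored messages without mHC.

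A smaller point has the same source. Session 1 is designed to build motivation, so a readiness score taken there may already reflect exposure to mHC.

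**Working it through.** The plan has no figure of its own for tailoring. Its power statement is not used here, and this point does not depend on it.

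**Inputs from the article.** Four cells of 25 (Table 1); effect coding −1/+1 (Data Analysis); readiness taken in mHC session 1 (MTM section).

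**Assumptions, not in the article.** Outcome SD of 1; messages in the MTM-only arm are untailored; t is the extra effect of tailored over untailored messages.

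**Cell means**, with a the mHC effect, b the untailored MTM effect and no true synergy:
- SAC: 0
- mHC+SAC: a
- MTM+SAC: b
- mHC+MTM+SAC: a + b + t

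**Contrasts.**
- mHC main effect = [(a − 0) + (a + b + t − b)]/2 = a + t/2
- MTM main effect = [(b − 0) + (a + b + t − a)]/2 = b + t/2
- Interaction (difference in differences) = (a + b + t) − a − b + 0 = t

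With true synergy s, the interaction contrast becomes t + s. Four cell means cannot identify five quantities (the SAC mean, a, b, t and s), so only the sum t + s is estimable.

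**Size against sampling error** (unadjusted, complete data). The standard error of the interaction contrast is √(4/25) = 0.40 SD. The standard error of a main effect is √(1/50 + 1/50) = 0.20 SD.

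| Assumed t (SD) | Interaction shift | Shift in each main effect | Shift in SE units (same for all three) |
|---|---|---|---|
| 0 | 0 | 0 | 0 |
| 0.2 | 0.2 | 0.10 | 0.5 |
| 0.3 | 0.3 | 0.15 | 0.75 |

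By normal approximation, a two-sided 5% test of an interaction with no true synergy rejects in about 8% of trials at t = 0.2 and about 12% at t = 0.3. As an outer bound, suppose tailored MTM has the planning effect f = 0.35 (d = 2 × 0.35 = 0.7) and untailored messages do nothing, so t = 0.7. The mHC main effect then rises by 0.35 SD, and the interaction test rejects in 41% of trials (noncentral F, 1 and 96 df).

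**Under the fix.** If both MTM arms are tailored from a common baseline score, the cells are 0, a, b + t and a + b + t. The interaction is (a + b + t) − a − (b + t) = 0, the mHC effect is a, and the MTM effect is b + t. If both arms get the same untailored messages, the three contrasts are a, b and 0. Either way t no longer depends on mHC level.

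**The case against.** A reader might infer that the MTM-only arm is known to receive untailored messages. The article does not say so. The MTM section also says in general terms that the delivery system tailors messages, and the full protocol, which is not shown, may define a default stream or a separate readiness check. This objection stands, so the consequence above is conditional. The conflict is not mere missing detail, however. The article names a source for the tailoring variable that its own Table 1 withholds from one arm. If the full protocol resolves this, the MTM section still needs correcting.

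t may also be small. Results describes four libraries organised by topic, with 76 messages and no mention of readiness, and adds only that "Refined MTM will be delivered to participants through SMS 2.0, an SMS text messaging platform". Daily messages for 2 months (about 60) plus weekly messages for 4 months (about 17) make roughly 77 sends. If messages are not repeated, which the article does not state, each participant would see nearly the whole set, leaving little room for content to differ. This too stands: zero belongs in the range.

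A reader might also call the factorial effects confounded. That goes too far. Randomisation still validly compares the four packages as delivered. If session 1 data make the messages better, the combination really does perform better, and dependence of this kind is part of what the trial sets out to examine. What is lost is attribution: tailoring cannot be told apart from any other synergy.

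Finally, this is a pilot with only preliminary selection, a further check on interactions and a fully powered trial planned later. That lowers the severity but does not remove the conflict.

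**Conclusion.** The point holds as a conflict between the tailoring rule and the factorial design. The rule cannot be followed in 25 of the 50 MTM participants, and what they receive is undefined. If their messages differ from those in the combined arm, the interaction contrast contains t and each main effect contains t/2.

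The algebra is exact for additive cell means, and it applies on the log-odds scale for viral suppression, the optimisation criterion. The SD figures are illustrations only. They assume a continuous outcome with SD 1, complete data and an untailored MTM-only arm. Over t = 0 to 0.3 SD, the shift is at most 0.75 standard errors in any of the three contrasts. At t = 0 there is no numerical bias, only an unspecified intervention.

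The documents do not support reading this as established bias or as a failure of the randomised comparison. The rating is should-fix.

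**What to change.** - **Preferred.** Add readiness-to-change items to the baseline computer-assisted interview for all participants. Randomisation already follows that interview, so the score precedes allocation. Drive tailoring from that value in both MTM arms (MTM+SAC and mHC+MTM+SAC).
- **Alternative.** Send the same untailored messages in both MTM arms.
- **Either way.** Reword the MTM section to match. Name the arms by content, because Table 1 and the Abstract number them differently: the combined arm is condition 1 in one and (4) in the other.
- **Participants already enrolled.** Phase 3 began in June 2025, so record which message version each participant received and report a sensitivity analysis by version.
- **If the rule cannot be changed.** State what the MTM-only arm receives, and interpret the interaction and both main effects as including tailoring.

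The cost is a few baseline items, a change in message routing and an amendment, with no extra participants or visits. The real downside is that changing the rule mid-trial creates two MTM versions by calendar time. The sensitivity analysis can describe this but, with 25 per arm, is unlikely to resolve it.
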